## Abstract

**Background:**

Mental disorders, including major depressive disorder (MDD), are a leading cause of non-fatal burden of disease globally. Current conventional treatments for depression have significant limitations, and there have been few new treatments in decades. The microbiota-gut-brain-axis is now recognised as playing a role in mental and brain health, and promising preclinical and clinical data suggest Faecal Microbiota Transplants (FMT) may be efficacious for treating a range of mental illnesses. However, there are no existing published studies in humans evaluating the efficacy of FMT for MDD.

**Methods and design:**

This protocol describes an 8-week, triple-blind, 2:1 parallel group, randomised controlled pilot trial (*n* = 15), of enema-delivered FMT treatment (*n* = 10) compared with a placebo enema (*n* = 5) in adults with moderate-to-severe MDD. There will be a further 26-week follow-up to monitor longer-term safety. Participants will receive four FMT or placebo enemas over four consecutive days. The primary aims of the study are to evaluate feasibility and safety of FMT as an adjunctive treatment for MDD in adults. Changes in gut microbiota will be assessed as a secondary outcome. Other data will be collected, including changes in depression and anxiety symptoms, and safety parameters.

**Discussion:**

Modification of the microbiota-gut-brain axis via FMT is a promising potential treatment for MDD, but there are no published rigorous clinical trials evaluating its use. If this study finds that our FMT strategy is safe and feasible, a larger fully powered RCT is planned. Further high-quality research in this field is urgently needed to address unmet need.

**Trial registration:**

Australian and New Zealand Clinical Trials Registry: ACTRN12621000932864

## Background

Mental disorders, including major depressive disorder (MDD), are a leading cause of non-fatal burden of disease globally [1]. Current evidence-based treatments for MDD (i.e. antidepressants and psychotherapy) have limitations including limited efficacy, side effects, and cost, as well as access issues in the case of psychotherapy. Moreover, the economic pressure of mental disorders supersedes that of cancer, diabetes, and cardiovascular diseases [2]. Thus, the development of affordable and novel treatments for MDD that can augment existing strategies would be of significant benefit to patients and their families, to the healthcare system, and to the broader economy.

### Microbiota-gut-brain-axis

There is a well-established association between mental health and the gut microbiota that co-exist symbiotically in our gastrointestinal tract, referred to as the ‘microbiota-gut-brain axis’ [3, 4]. There are data linking various biological variables to the aetiology and maintenance of MDD; these have been extensively reviewed elsewhere, and include inflammatory mediators (e.g. elevations in c-reactive protein and inflammatory cytokines), metabolic factors (e.g. insulin resistance, metabolic syndrome), oxidative stress (e.g. reactive oxygen species and mitochondrial dysfunction), the hypothalamic-pituitary-adrenal (HPA)-axis (e.g. perturbations in cortisol), neurotransmitters (e.g. gamma-aminobutyric acid and serotonin precursors), neuropeptides (e.g. brain-derived neurotrophic factor (BDNF)), and other systems [3, 5]. Each of these systems are potentially influenced by the gut microbiota, and emerging evidence linking gut microbiota to brain and behaviour suggests that the gut may be a key modifiable target for mental and brain health [3].

### Evidence for the potential role of gut microbiota in treating MDD

Differences in gut microbiota composition have been observed in depressed compared to non-depressed humans across several studies [4, 6–10]. Commonalities across studies include increased lactic acid producing bacteria such as *Lactobacillus*, *Streptococcus*, and *Enterococcus*, and reductions in bacteria with the capacity to produce the short-chain fatty acid butyrate, such as *Faecalibacterium* and *Coprococcus* [4, 11]. Additionally, there appears to be evidence of correlations between specific gut bacteria and depression symptomatology [4, 12]; however, few studies have explored this link, and the associations between MDD symptomatology, gut microbiota composition, and their functional potential are poorly understood.

Further to this, there is evidence supporting the potential efficacy of probiotics for depression and anxiety [13]. Meta-analyses of studies investigating probiotic supplementation as an adjunctive treatment for depression suggest that this treatment strategy may be effective for the reduction of depressive symptoms, particularly in those with clinical depression [14, 15], or alongside antidepressant therapy [16]. However, these treatments are limited to a single bacterial strain or, at best, a small number of strains. Conversely, faecal microbiota transplant (FMT), which encompasses a complete human gut microbiome containing thousands of potentially symbiotic strains [17], may have the potential to more effectively alter the composition of the gut microbiota, thus the influence of FMT on mental health symptoms warrants further exploration.

### preclinical evidence supporting a trial of FMT for MDD

Experimental studies in rodents suggest that alterations of microbial composition of the gut via FMT can induce changes in behaviour [18, 19] and influence rodent models of psychiatric disorders [20]. A seminal study by Kelly et al. [7] provided the first evidence that the transfer of faecal matter from individuals with MDD into germ-free rodents could induce depression-like behaviours in the rodents, as well as other physiological features associated with depression such as changes in tryptophan metabolites. Remarkably, four further studies have now shown that the transfer of faeces from depressed humans into microbiota-depleted mice induces depression-like behaviours in the mice [21–24], and similar outcomes have also been observed in rodent models of schizophrenia [25]. Together, these preclinical studies provide foundational evidence of the potential utility of FMT for depression.

### Evidence for FMT in neuropsychiatric disorders in humans

In humans, FMT is an established treatment for *Clostridioides difficile* infection (CDI) [26, 27], with a cure rate of 80–90%. It has also shown potential in a variety of other conditions [28–30], including gastrointestinal [31–35], autoimmune [36, 37], antibiotic-resistant organisms, hepatic disorders, metabolic [38, 39], and neuropsychiatric conditions [40, 41] including autism spectrum disorder [41]. Whilst to date no large scale studies in humans have investigated the use of FMT for psychiatric disorders, case studies suggest promising outcomes with respect to the treatment of depressive symptoms [42, 43] and bipolar disorder [44, 45]. Studies of FMT in people with irritable bowel syndrome [IBS]—which is commonly comorbid with psychiatric symptoms—have also shown improvements in mental health symptomatology [28, 40, 46, 47]. Case studies have also reported a reduced need for antidepressant medications in IBS patients post-FMT [48].

### safety of FMT

The safety of FMT has been established across multiple patient populations [29], including immunocompromised [49] and paediatric populations [50], and over the long term [51]. Other studies have demonstrated FMT to be safe even in healthy recipients, not merely those with CDI and other health disorders [52]. Indeed, adverse reactions are rare and appear to be more frequently associated with delivery method [53–55] or the underlying disorder and/or symptoms for which FMT is being used [28], rather than the FMT itself. Indeed, our recent systematic review and meta-analysis of FMT studies for conditions other than CDI found more serious adverse events reported in the placebo group than in the group receiving the FMT intervention [28]. Of the adverse events observed in participants allocated to FMT, all but one such event was deemed unlikely to be related to the FMT. Moreover, rates of mild to moderate adverse events were similar between participants receiving FMT and those who received placebo.

Whilst most FMT studies report only mild and self-limiting adverse events [56], in 2019 a warning regarding the risks of FMT was released by the US Food and Drug Administration (FDA). This warning was in response to a death that occurred in an immunocompromised patient who received unscreened donor faeces containing antibiotic-resistant organisms, specifically, extended spectrum beta lactamase-producing *Escherichia coli*. This serious incident highlights the importance of adhering to rigorous donor screening protocols including screening thoroughly for antibiotic-resistant organisms. In Australia, the practice of FMT is now regulated by the Therapeutic Goods Administration (TGA), which includes strict, detailed, and comprehensive standards for the manufacture and supply of FMT. The FMT used in this study (the “Moving Moods Pilot Study”) utilises a product that meets the TGA standards.

## Methods

### Objectives

The primary objectives for this study are to evaluate the feasibility and safety of FMT as an adjunctive treatment for MDD in adults. The secondary objective is to evaluate the impact of enema-delivered FMT on gut microbiota compared with a placebo enema in adults with MDD. As this study is not powered to evaluate efficacy, exploratory objectives include any changes observed in depression and anxiety symptoms, sleep, quality of life, level of function, gut symptomatology, blood biomarkers of neurogenesis, gut permeability, inflammation, and cardiometabolic parameters following delivery of FMT via enema compared with a placebo enema in adults with depression.

### Study design

This study is an 8-week, triple-blind, 2:1 parallel group, randomised controlled pilot trial (*n* = 15), of enema-delivered FMT (*n* = 10) compared with a placebo enema ( *n*= 5) in adults with moderate-to-severe MDD. There will be a further 26-week follow-up for safety data.

### Study intervention

Participants will receive a total of four doses of an FMT via enema (henceforward referred to as ‘active’), or four doses of placebo enema, as an adjunct to treatment as usual. The active FMT enema will comprise of syringes supplied by BiomeBank containing a total volume of 50 mL including 12.5 mg donor faeces: normal saline (0.9%) and 10% glycerol. The FMT was prepared in accordance with the Australian TGA standards which are described in detail on the TGA website (TGO-105: Standards for FMT) [57]. Briefly, anonymous, fit, and healthy volunteers aged 18–60 years undergo a rigorous screening process prior to donation, including a thorough medical interview and examination by a physician, and the collection of donor biological samples (stool, blood, and nasal swab) to ensure the absence of viral, bacterial, and parasitic pathogens. For a full overview of the donor screening process, see reference [58] (TGO-105: Standards for FMT) [57]. The placebo will consist of a visually identical placebo product containing a total volume of 50 mL including normal saline; 10% glycerol, and brown dye.

### Procedure

Participants will receive either four active or four placebo FMT delivered via an enema will be administered over four consecutive days to each participant by a research nurse. Assessments will be conducted at baseline, and then every 2-weeks until the primary end point (8 weeks). A further follow-up assessment will then occur at week 26 to capture long-term safety data. An outline of the study schedule is provided in Table 1 and the appointment schedule is summarised in Fig. 1. Participants, investigators, assessors, and study statisticians will be blinded to group allocation. This protocol is reported as per the Standard Protocol Items: Recommended for Intervention Trials (SPIRIT) guidelines [58], and the CONSORT extension for pilot and feasibility trials checklist [59]. All study procedures will be concordant with Good Clinical Practice (GCP) principles. The consent procedure is described below under the heading Consent and Enrolment.

**Table 1 Tab1:** Schedule of assessments, instruments, and procedures to be implemented at each study appointment

Variable	Instrument	*Week (first row)* Appointment number (second row)										
		*− 2*		*0 (baseline)*				*2*	*4*	*6*	*8*	*26*
		1a	1b	2	3	4	5	6	7	8	9	10
Screening (via Telehealth)												
Enrolment	Informed consent	✓										
General inclusion criteria	Eligibility screener for entrance criteria	✓										
Alcohol and substance abuse	Alcohol Use Disorders Identification Test (AUDIT) Drug Abuse Screening Test (DAST-10)	✓										
Diagnosis of MDD	Structured Clinical Interview for the DSMI-V (SCID-V) mood disorders module		✓									
Depression severity and suicidality	Montgomery-Asberg Depression Rating Scale (MADRS)		✓									
Study appointments												
Group allocation	Randomisation spreadsheet			✓								
FMT	Enema-delivery of intervention or placebo			✓	✓	✓	✓					
Demographics	General questionnaire			✓								
Medical history	Medical history Standard psychiatric assessment Family history		✓ (optional)	✓								
Study appointments continued.												
Medication use	Current medications Medication history		✓	✓								
Personality disorders	Personality disorders (SAPAS)			✓								
Diet	Diet (Simple Dietary Questionnaire)			✓							✓	
Psychological symptoms	Depression, Anxiety and Stress symptomatology (DASS) Depression severity (MADRS) Suicidality (MADRS)			✓				✓	✓	✓	✓	
Gut symptoms	Gastrointestinal Symptom Rating Scale (GSRS)			✓				✓	✓	✓	✓	
Medical variables	Change in medications, vaccines, illness, etc			✓				✓	✓	✓	✓	
General health and functioning	Patient Global Impression of Change Sheehan Disability Scale Sleep (Pittsburgh Sleep Quality Index) Quality of Life			✓				✓	✓	✓	✓	
Study appointments continued.												
Changes of circumstance	Medication changes questionnaire			✓				✓	✓	✓	✓	
Cost analysis	Resource Utilisation Questionnaire			✓							✓	
Physical examination	Height (stadiometer) Weight (scales) Blood pressure (sphygmomanometer) Heart rate (sphygmomanometer)			✓				✓			✓	
Blood samples	Whole blood by research nurse/ACL			✓				✓			✓	
Stool samples	Microba stool collection kits			✓				✓			✓	
Feasibility data												
Tolerability	Adverse events			✓	✓	✓	✓	✓	✓	✓	✓	✓
Adequacy of blinding	Participant questionnaire							✓				
Adherence	Monitoring questionnaire completion and appointment attendance throughout the study period			✓	✓	✓	✓	✓	✓	✓	✓	
Acceptability	Study Participant Feedback Questionnaire Specific questions pertaining to study intervention			✓				✓			✓	
Researcher/trial feasibility data												
Recruitment	Monitoring of recruitment rates by study staff throughout trial period			✓	✓	✓	✓	✓	✓	✓	✓	
Retention	Monitoring of trial attrition by study staff throughout trial period			✓	✓	✓	✓	✓	✓	✓	✓	

The study schedule allows for flexibility for all or parts of each appointment to be conducted by telehealth if this is preferable to the participant or required for other reasons

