### Primary outcome measures

The primary outcomes for this study are (1) the feasibility and (2) safety of FMT as an adjunctive treatment for MDD in adults. The study outcomes, participant appointment schedule, and study timeline are outlined in Table 1 and Fig. 1.

Feasibility will be considered as a composite outcome, measured by the following:The ability to meet recruitment targets (measured by recruitment logs, comparing actual recruitment against projected targets)Participant retention and completion rates (measured by attrition rates and completeness of data)Adherence to intended protocol (measured by completion of intervention as planned, missed appointments, technical difficulties arising, and completeness of study data)Participant acceptability (measured using the TransCelerate Study Participant Feedback Questionnaire, plus the addition of questions designed specifically for this study)Robustness of study methodology, including effectiveness of blinding (measured qualitatively based on feedback from researchers throughout and at the conclusion of the study, and a participant and researcher survey to assess blinding)

Safety of FMT as an adjunctive treatment in adults will be measured by an assessment of adverse events. These data will be collected through direct observations by the study nurse during administration of the intervention, and via participant reporting during the intervention and each appointment thereafter (measured at weeks 0, 2, 4, 6, 8, and 26). Participants will also be encouraged to contact the research team at any time to report adverse events outside of study appointments.

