
### Feasibility targets

Table 4 outlines pre-specified targets identified by the research team as a minimum standard that would indicate that the study design was feasible. These targets will also assist the study team to identify aspects of the trial that may need to be amended to improve future, large-scale trials.

**Table 4 Tab4:** Feasibility targets

Target area	Feasibility target
Recruitment	Successful enrolment of *n* = 15 participants across a 6-month active recruitment period
Retention	A minimum of *n* = 10 participants to complete study until the 8-week primary endpoint (i.e. a 33% attrition rate).
Adherence to protocol	Participants should: 1) Receive two of the total four enemas 2) Attend their baseline, week 2 and week 8 appointments 3) Provide baseline and week 2 stool samples
Safety	Nil severe and/or serious adverse events rated as likely due to study intervention in the active FMT group.
Adequacy of blinding	The best achievable outcome for adequacy blinding is participants and researchers correctly guessing allocation at a rate of 50% (the rate due to chance). Whilst we are not likely to be statistically powered to measure this outcome, we aim to reach an outcome approaching 50%.

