### Impact of and response to participant withdrawal

Participants will be withdrawn from the study if they withdraw consent or at the discretion of the researcher given adverse events or loss to follow-up. Reasons for withdrawal will be documented, and participants will be asked whether they are willing to accept any further contact to assess short- and longer-term safety.

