## Discussion

Despite the promising body of evidence and biological rationale to support the efficacy of FMT in MDD, the known relationship between intestinal dysbiosis and MDD [7, 23, 66–68], and the established efficacy of FMT in altering intestinal microbiota [69–71], there have been no published studies to date examining the impact of FMT on MDD in humans. FMT may represent a safe, fast, and effective way of treating MDD. This is potentially highly significant given the enormous psychosocial and economic burden of depression, and the limitations of existing treatment options. These factors provide compelling support for investigating the use of FMT in MDD.

As described above, substantial phase I evidence already exists for the safety of FMT across a broad range of indications [29], including immune-compromised populations [49] and in the long term [51]. This study is the first randomized, triple-blind, placebo-controlled feasibility trial assessing the feasibility, tolerability, and acceptability of FMT in the treatment of MDD in adults.

The present study has a long follow-up period (6 months), allowing for longer-term safety data and monitoring. The results of the present study will have multiple applications. Firstly, if the study is found to be feasible, they will be used to support and inform a fully powered efficacy study, which will also utilise a randomised, triple-blind, placebo-controlled design. Secondly, the study will allow us to determine whether enema-delivered FMT is acceptable to people with depression; this is important given the nature of this intervention, with the requirement to attend a clinic on four consecutive days to receive an intervention. Thirdly, assessing changes in gut microbiota and the degree to which any gut microbiota changes are concordant with the donor microbiota may yield useful information regarding dosing and frequency. Moreover, examination of possible biomarker changes that are linked to MDD, and in many cases the gut microbiota, may yield insights into mechanistic processes prompted by FMT. Fourth, although not powered to detect efficacy endpoints, some initial suggestions of potential changes in symptomatology and measures of well-being and functioning may be useful in understanding the sample size required for a scaled RCT. Finally, collecting and analysing initial cost-efficacy data will also inform the next steps in the application of this intervention in a clinical setting.

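### Participants who leave the study before week 2 give no scheduled acceptability rating after the first enema day, so the questionnaire result may be too favourable

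*Protocol article*

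**What the plan says.** The section on primary outcome measures makes feasibility a composite of five components. One is "Participant acceptability (measured using the TransCelerate Study Participant Feedback Questionnaire, plus the addition of questions designed specifically for this study"). Retention and adherence are two of the others.

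The Procedure section says the enemas "will be administered over four consecutive days to each participant by a research nurse"; these are appointments 2 to 5 in Table 1. The acceptability row of that table, "Study Participant Feedback Questionnaire Specific questions pertaining to study intervention", is ticked at appointment 2 (week 0), appointment 6 (week 2) and appointment 9 (week 8). It is not ticked at appointments 3 to 5, where adverse events, adherence and retention are. A note under the table allows all or part of any appointment to be held by telehealth.

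On withdrawal, the reasons are recorded and "participants will be asked whether they are willing to accept any further contact to assess short- and longer-term safety". Acceptability is not named as a purpose of that contact.

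Table 4 sets no target for acceptability. The feasibility analysis is described as a qualitative synthesis. The Discussion nevertheless states that "the study will allow us to determine whether enema-delivered FMT is acceptable to people with depression", and links this to the demand of attending on four consecutive days.

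**The concern.** The burden in question is the four-day course. The week 0 form is completed on the first enema day, so it can reflect one enema at most, and the article does not say whether it is given before or after that enema. The first form that can cover the course as received is at week 2. A participant who leaves in between has no scheduled opportunity to rate it.

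If people leave in that window because of the enemas, the missing answers depend on the very thing being measured, and the remaining answers lean towards the favourable side. The result is meant to support a larger trial with the same or a similar product and protocol. An acceptability conclusion drawn mainly from people who stayed would be least reliable in the situation where it matters most.

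**Working it through.** **1. Placing the ticks.** Table 1 has 11 appointment columns (1a, 1b, 2 to 10). Reading the acceptability row against them gives ticks at 2, 6 and 9 and none elsewhere. Combined with the withdrawal section, this gives:

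| Participant | Scheduled rating after the first enema day? |
|---|---|
| Leaves the study during enema days or before week 2 | No |
| Stops enemas, stays in the study | Yes, weeks 2 and 8 |
| Completes the course, leaves after week 2 | Yes, week 2 |
| Completes the study | Yes, weeks 2 and 8 |

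Only the first row is affected.

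**2. The plan's own figure.** The design is an "8-week, triple-blind, 2:1 parallel group, randomised controlled pilot trial" with 15 participants, 10 active and 5 placebo. Table 4 asks for at least 10 "participants to complete study until the 8-week primary endpoint (i.e. a 33% attrition rate"). Check: (15 − 10)/15 = 33.3%, which reproduces the stated 33%.

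**3. Weight of one person.** 1/15 = 6.7%, about 7 points.

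**4. Illustration.** The article gives no acceptability rate, threshold or denominator, and no figure for losses before week 2. The following rests on assumptions. Let k participants leave before week 2.

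*Extreme case:* every early leaver found the enemas unacceptable and every responder found them acceptable. Responders show 100%; the share among all 15 is (15 − k)/15.

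- k = 0: 15/15 = 100%, overstatement 0 points
- k = 1: 14/15 = 93%, overstatement 7 points
- k = 3: 12/15 = 80%, overstatement 20 points
- k = 5: 10/15 = 67%, overstatement 33 points

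*Varying the reason for leaving:* k = 5, and 8 of the 10 responders (80%) find the enemas acceptable. Suppose m of the 5 leavers left because the enemas were unacceptable and the rest would have answered as responders did. The share among all 15 is [8 + 0.8 × (5 − m)]/15.

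- m = 0: 12/15 = 80%, overstatement 0 points
- m = 2: 10.4/15 = 69%, overstatement 11 points
- m = 5: 8/15 = 53%, overstatement 27 points

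The value k = 5 is the whole week 8 retention allowance. It is reached before week 2 only if every tolerated loss happens that early.

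**The case against.** A reader might infer that everyone who stops the enemas disappears from the acceptability measure. The article does not support that. Table 4 requires participants to "Receive two of the total four enemas" and to attend baseline, week 2 and week 8, so partial dosing with continued follow-up is foreseen. Such a person is asked at weeks 2 and 8, possibly by telehealth. Declining an enema is not listed among the grounds for withdrawal.

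A reader might also treat the five tolerated losses as five missing ratings and set, say, 9/10 = 90% against 9/15 = 60%. That needs all five to leave before week 2, all because of the enemas. It also turns acceptability into a percentage that the article never defines. Anyone leaving between weeks 2 and 8 has already been asked at week 2.

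The early leavers are not invisible either. Their reasons are recorded, and their departure counts under retention and adherence within the same composite. In a qualitative account of 15 people, one person leaving because of the enemas would probably be noticed. Finally, denominators and summaries are often left to an analysis plan.

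All of this stands, and it narrows the point. What it does not remove is the collection gap, which the article itself fixes through the visit schedule and the stated purpose of contact after withdrawal. Retention shows that someone left, and a recorded reason may show why. Neither is a rating of the intervention, and nothing says either feeds the acceptability result. A qualitative synthesis cannot use views that were not collected.

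**Conclusion.** The point holds for one group: participants who leave the study during the enema days or before week 2. They give no scheduled acceptability rating after the first enema day, so those most likely to have found the enemas unacceptable are under-represented in one component of the primary outcome. An upward bias is plausible but not certain, because it depends on leavers having disliked the enemas more than those who stayed.

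Its size cannot be derived from the document. Under the assumptions shown it runs from 0 to 33 points, and the upper end is an extreme case. The feasibility composite as a whole is less exposed than the questionnaire, because the leavers count elsewhere in it. This is a cheap improvement to a design choice; no contradiction or wrong figure in the protocol is involved.

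**What to change.** Three small changes:

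1. Give the existing intervention-specific acceptability questions at the last enema visit attended or, failing that, at withdrawal.
2. In the section on participant withdrawal, extend the further contact, with consent, to acceptability as well as safety.
3. Report acceptability with the number responding out of everyone who received at least one enema, next to the documented reasons for withdrawal.

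Counting every non-responder as having found the enemas unacceptable is not needed. It would bias the result downward for people who left for unrelated reasons.

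The cost is one short existing questionnaire at a visit or contact that already takes place. The downside is a small extra burden on people who are leaving and a possibly less favourable result.
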